# The iGreenGO Study: The Clinical Role of Indocyanine Green Imaging Fluorescence in Modifying the Surgeon’s Conduct During the Surgical Treatment of Advanced Gastric Cancer—Study Protocol for an International Multicenter Prospective Study

**DOI:** 10.3389/fonc.2022.854754

**Published:** 2022-03-17

**Keywords:** gastric cancer, advanced, indocyanine green (ICG), surgery, D2 lymphadenectomy, surgical conduct

## Abstract

**Background:**

The near-infrared/indocyanine green imaging fluorescence (NIR/ICG) technology is showing promising results in several fields of surgical oncology. The clinical value of NIR/ICG technology in the surgical treatment of advanced gastric cancer (AGC) is not clearly established.

**Methods:**

This is the protocol of the “iGreenGO” (indocyanine Green Gastric Observation) Study, a national prospective multicenter study. Western patients who undergo curative-intent gastrectomy with D2 lymphadenectomy for AGC constitute the study cohort. All the patients undergo preoperative upper gastrointestinal endoscopy for submucosal peritumoral ICG injection at the most 20 h before surgery. Intraoperative endoscopic injection before starting surgical dissection is also allowed. The primary endpoint is the “change in the surgical conduct” (CSC), i.e., the need to perform further dissection after intraoperative NIR/ICG technology activation at the end of D2 lymphadenectomy. Secondary endpoints include the pattern of abdominal fluorescence distribution according to tumor and patient characteristics, the preoperative clinical variables potentially associated with CSC, and the incidence of stage migration due to NIR/ICG application.

**Discussion:**

The iGreenGO Study is the first study to investigate the clinical role of NIR/ICG technology for the surgical treatment of AGC in a large cohort of Western patients. Results from the present study can further clarify the role of NIR/ICG technology in surgical lymphadenectomy for AGC.

## Background

Gastric cancer accounts for 5.7% of all neoplasms in both sexes. It is the fifth most common and the third most lethal tumor in Europe, with a 5-year overall survival (OS) rate of 25% (1, 2).

Although several (neo)adjuvant treatments have been developed to improve survival outcomes (3), surgery remains the mainstay of treatment of resectable gastric cancer and the only curative option (4).

Surgical intervention was traditionally performed *via* laparotomy; however, the minimally invasive approach has gained attention over the last decade, demonstrating better short-term outcomes (e.g., lower blood losses, reduced postoperative pain, and reduced hospital stay) (5, 6) and comparable long-term oncological outcomes (7) as compared with the open approach.

Regardless of the surgical approach, margin-negative resection and adequate lymphadenectomy are the major treatment-related prognostic factors (4).

In patients with resectable advanced gastric cancer (AGC), the Japanese Gastric Cancer Association (JGCA) guidelines (4, 8) recommend D2 lymphadenectomy, consisting in the removal of the lymph nodes (LNs) along the left gastric artery, the common hepatic, the splenic artery, and the coeliac axis, in addition to the perigastric LNs (9). In carefully selected patients, a nodal dissection beyond the D2, the so-called D2+ lymphadenectomy, is recommended (9).

Since nodal involvement is one of the most important prognostic factors for OS and disease-free survival (DFS) (10, 11), several efforts have been made to help the surgeon to optimize lymphadenectomy. Among these, the application of indocyanine green (ICG) together with light at wavelengths in the near-infrared range (NIR) is showing interesting results.

ICG is a fluorescent cyanine dye approved for medical uses by the FDA in the late 1950s. Administered intravenously or through submucosal visceral injection, it allows the visualization of anatomical structures (12). Injected in any tissue (submucosal visceral, intramammary, intracutaneous, etc.), ICG binds to interstitial proteins (albumin, globulins, etc.) and enters the lymphatic vessels of the injected site. So, fluo-labeled “proteins” are taken up by the reticuloendothelial cells in the lymph nodes on the lymphatic draining pathways. The absorption and fluorescence spectrum of ICG is in the NIR region (wavelength 800–1,000 nm) and can be visualized by dedicated infrared-based cameras. ICG has low autofluorescence and high tissue penetration by the wavelengths of the penetrating laser (which excites the ICG), providing better contrast in real-time structure visualization during surgical intervention; for these reasons, over the last years, its use has been preferred over other fluorescent contrast agents, such as methylene blue and fluorescein, which have lower wavelengths (700 and 520 nm, respectively) and therefore suboptimal characteristics for surgical visualization (13).

NIR fluorescence imaging with ICG (defined as “NIR/ICG technology” hereinafter) has been introduced in many surgical fields (14): in colorectal surgery, it is used for the evaluation of real-time visceral perfusion with the aim to reduce the rate of anastomotic leaks (15); in hepatobiliary surgery, it allows the visualization of the biliary structures and the evaluation of liver function (16); and in melanoma and breast cancer surgery, it might be used for sentinel LN detection (17, 18).

In the field of gastric cancer surgery, the NIR/ICG technology was firstly applied in Eastern countries for sentinel LN detection in patients with early gastric cancer (EGC) (19). In Western countries, where the different tumor biology and the absence of a screening program lead to a higher rate of ACG with nodal involvement at first diagnosis (20), the NIR/ICG technology was rather used for abdominal nodal mapping (21, 22) showing promising results in the assessment of lymphadenectomy thoroughness (23–26). However, all the studies investigating NIR/ICG technology focused on its ability to increase the number of harvested LNs, while no data exist regarding its potential role in changing the surgical conduct at the moment of lymphadenectomy (27) allowing an improvement in lymphadenectomy as compared with lymphadenectomy performed without the use of any technology; in addition, no data exist about the role of this hypothetical lymphadenectomy improvement on tumor staging and the subsequent treatment planning.

## Material and Methods

### Objective

The iGreenGO Study aims to investigate whether the intraoperative application of NIR/ICG technology is associated with a change in the surgical conduct (CSC) during curative-intent gastrectomy with D2 lymphadenectomy in a cohort of Western patients affected by AGC.

The preoperative clinical variables potentially associated with CSC will be also investigated.

### Study Design and Setting

The iGreenGO Study is a single-arm prospective observational multicentric study. National and international academic and non-academic hospitals are invited to participate in the study. The duration of the study will be approximately 4 years (3 years for inclusion, 1 year for data analysis and results publication). The enrolment of patients has started since September 2021.

All procedures will be in accordance with the ethical standards of the responsible committee on human experimentation (institutional and regional) and with the Helsinki Declaration of 1975, as revised in Brazil 2013 (28). The Local Ethical Committee reviewed and approved the protocol (380-09062021). The protocol is registered at *clinicaltrial.gov* (NCT04943484). Study results will be reported according to Strengthening the Reporting of Observational Studies in Epidemiology (STROBE) statements (29).

### Study Population

This study includes all patients affected by advanced resectable (cT2–T4a, N0–3, M0) gastric adenocarcinoma.

### Inclusion Criteria

In order to be eligible to participate in this study, a patient must meet all of the following criteria:

- Age ≥18 years old- Preoperative histologically proven primary adenocarcinoma of the upper, middle, or lower part of the stomach- Advanced disease (staged cT2–T4a, N0–3, M0 according to the eighth edition of the AJCC TNM Staging System) at diagnosis, in which curative resection can be safely achieved by distal or total gastrectomy with D2 lymphadenectomy *via* a minimally invasive (robotic or laparoscopic) approach, either as first treatment or after neoadjuvant treatment- Written informed consent signed to preoperative endoscopy and surgical intervention

### Exclusion Criteria

Patients presenting one or more of the following conditions will not be eligible to participate in the iGreenGO Study:

- Previous abdominal surgery interfering with lymphatic drainage of the stomach, including previous gastrectomy, endoscopic mucosal resection, or endoscopic submucosal dissection- Conversion to laparotomy during surgical dissection for any reason- Cancer located at the esophagogastric junction [Siewert I, II, III tumors (30)]- Patients who are candidates for transthoracic esophagectomy, transhiatal extended gastrectomy, or proximal gastrectomy- Distant metastases and/or direct invasion of the pancreas, spleen, or other adjacent organs at the preoperative and intraoperative examination- History of allergy to iodine agents- Women during pregnancy or breastfeeding

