### Endpoints

The primary endpoint is the CSC at the moment of intraoperative NIR/ICG technology activation after D2 lymphadenectomy performed with the “naked eye.”

The secondary endpoints are the preoperative clinical variables potentially associated with CSC. The other secondary endpoints are as follows: the pattern of abdominal fluorescence distribution according to tumor and patient characteristics, the number of additional lymph nodes retrieved using NIR/ICG technology, the incidence of stage migration due to NIR/ICG application, and the 90-day morbidity and mortality.

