**Figure 1 f1:**
[figure not shown]
Summary steps of the iGreenGO study. NIR/ICG, near-infrared/indocyanine green.

Patients undergo upper GI endoscopy at any time between 20 h before and the initiation (skin incision) of the planned surgery. The ICG powder (Verdye**
^®^
** 5 mg/ml, 25 mg powder for solution for injection, Diagnostic Green, Aschheim-Dornach, Germany) is dissolved in sterile water, obtaining a final concentration of 0.125 mg/ml. Two milliliters of the obtained solution is injected in the submucosa with a 23-gauge endoscopic needle (introduced through the flexible scope working channel) into four peritumoral sites, 0.5 ml for each site. In the case of stenotic cancers, ICG injection can be performed at four proximal tumor points.

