### Step 3: Surgical Intervention and Lymphadenectomy

The type of surgical resection is assessed according to the tumor site and is accomplished according to JGCA guidelines (9).

More specifically:

- Distal gastrectomy (DG) with D2 lymphadenectomy includes the resection of two-thirds of the stomach including the pylorus and dissection of 1, 3, 4sb, 4sd, 5, 6, 7, 8a, 9, 11p, and 12a lymph node stations.- Total gastrectomy (TG) with D2 lymphadenectomy includes the total resection of the stomach including the cardia and pylorus and dissection of 1, 2, 3, 4sa, 4sb, 4d, 5, 6, 7, 8a, 9, 11p, 11d, and 12a lymph node stations.

Digestive tract reconstruction can be accomplished *via* a mini-laparotomy through an abdominal incision not greater than 10 cm. Any abdominal incision greater than 10 cm will be classified as a conversion to open approach, as well as any need to complete the resection phase by any type of laparotomy. A specific sequence of D2 nodal station dissection is not mandatory; the D2 lymphadenectomy technique described by Giacopuzzi et al., which is based on the takeover of specific vascular landmarks, is used in most participating centers (37).

Surgical resection with D2 lymphadenectomy is performed “with the naked eye,” which means using conventional white-light imaging visualization without application of NIR/ICG technology.

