### Step 4: Intraoperative Application of NIR/ICG Technology (Second Time) and Definition of CSC

At the end of D2 lymphadenectomy “with the naked eye,” a visualization of the operative field is performed using NIR/ICG technology in order to verify the presence of residual LN in each D2 nodal station.

The CSC is defined in the case of persistence of fluorescence in one or more D2 nodal stations after the completion of D2 lymphadenectomy performed with the “naked eye,” requiring further dissection to remove the residual D2 nodal fluorescent structures.

The nodal stations dissected after NIR/ICG visualization are also recorded.

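### Conversion to laparotomy during dissection is an exclusion criterion although it arises after ICG injection, so the rule can remove patients already scored CSC-positive and drops converted patients from 90-day morbidity and mortality

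*Protocol article*

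**What the plan says.** The Exclusion Criteria open with "Patients presenting one or more of the following conditions will not be eligible to participate in the iGreenGO Study", and one of the listed conditions is "Conversion to laparotomy during surgical dissection for any reason".

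The order of events comes from other sections:

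- **Consent** to endoscopy and surgery is an inclusion criterion (Inclusion Criteria).
- **Injection** (Step 1): "Patients undergo upper GI endoscopy at any time between 20 h before and the initiation (skin incision) of the planned surgery".
- **Second NIR look** (Step 4): after the white-light D2 lymphadenectomy, "a visualization of the operative field is performed using NIR/ICG technology in order to verify the presence of residual LN in each D2 nodal station". CSC is positive when residual fluorescence in a D2 station requires more dissection.
- **Reconstruction** (Step 3) may use a mini-laparotomy of up to 10 cm. On larger incisions the section says: "Any abdominal incision greater than 10 cm will be classified as a conversion to open approach". A laparotomy needed to complete the resection phase also counts as conversion.

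CSC is the primary endpoint. The secondary endpoints (Endpoints) include "the incidence of stage migration due to NIR/ICG application, and the 90-day morbidity and mortality".

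**The concern.** Eligibility depends on something that happens during the operation. A converted patient has been consented, injected and at least partly operated on before the rule applies.

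The extra dissection after a positive second look is still surgical dissection, and only CSC-positive patients have it. A conversion during that step makes a patient ineligible after the primary endpoint has been scored. By this route the rule can remove events but never non-events.

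The safety endpoints are affected too. The extra dissection is the surgical step that the technology adds. If it led to a conversion, that patient's 90-day outcome would leave the denominator, and the study could not see that harm. A larger sample would not correct this.

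**Working it through.** **1. The plan's own figure.** Table 1 sets N by the Wilson half-width:

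d = z·√n/(n+z²) · √(p(1−p) + z²/(4n)), with z = 1.96.

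At p = 0.17 and n = 217: 1.96 × 14.73/220.84 × √(0.1411 + 0.0044) = 0.1307 × 0.3815 = 0.0499. This matches the stated 5%. At n = 337 the half-width is 0.0401, against the stated 4%. All 63 cells of Table 1 reproduce within 2 patients, so the point does not rest on an error there.

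**2. Can conversion follow the CSC score?** The sequence is consent, injection, white-light D2 dissection, second look (CSC scored), further dissection if CSC-positive, reconstruction. The exclusion covers conversion during dissection, so it covers the further dissection. The answer is yes.

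**3. Possible effect on the CSC rate.** The conversion rate, its timing and the CSC frequency in converted patients are not in the documents. The assumptions are N = 217, a conversion rate of 5% or 10%, about half of conversions after the second look, and 17% CSC in retained patients.

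- 5%: 11 converted, 206 retained, 0.17 × 206 = 35 CSC, 5 conversions after the look.
- 10%: 22 converted, 195 retained, 0.17 × 195 = 33.15 CSC, 11 conversions after the look.

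Rate among all assessed = (CSC in retained + q × conversions after the look)/(retained + conversions after the look), where q is the CSC frequency in patients converted after the look.

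| q | 5% conversion | 10% conversion |
|---|---|---|
| 0.17 | (35+0.85)/211 = 17.0% | (33.15+1.87)/206 = 17.0% |
| 0.50 | (35+2.5)/211 = 17.8% | (33.15+5.5)/206 = 18.8% |
| 1.00 | 40/211 = 19.0% | 44.15/206 = 21.4% |

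The retained patients show 17.0% throughout, so the understatement runs from about 0 to 2.0 points (5%) or 4.4 points (10%). If q were below 0.17 the sign would reverse slightly: at q = 0 the rates are 35/211 = 16.6% and 33.15/206 = 16.1%.

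If only 20% of conversions follow the look and all are CSC-positive, the rates are (35+2.2)/208.2 = 17.9% and (33.15+4.4)/199.4 = 18.8%.

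**4. Bounds over all operated patients.** With CSC unknown in every converted patient, the overall rate is (1−c) × 17% + c × q, for q from 0 to 1:

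- c = 5%: 16.2% to 21.2%.
- c = 10%: 15.3% to 25.3%.

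**5. Possible effect on 90-day outcomes.** All rates here are assumed.

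- Morbidity 20% without and 45% with conversion: 0.95×20 + 0.05×45 = 21.3%, and 0.90×20 + 0.10×45 = 22.5%. Reporting 20% understates by 1.3 to 2.5 points.
- Morbidity 25% without and 25-50% with conversion, at 10% conversion: 25.0% to 27.5%.
- Mortality 2% without and 2-8% with conversion, at 10% conversion: 2.0% to 2.6%.

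**The case against.** The restriction has a basis in the design. Surgery in this study is minimally invasive only, the NIR system works through the surgical endoscope, and CSC is defined only after a completed white-light D2 dissection. For a conversion before the second look, CSC as defined may not be observable. This stands: some loss for the primary endpoint cannot be avoided. It does not explain removing patients already scored, or removing anyone from the 90-day outcomes. The Inclusion Criteria already restrict the population, before surgery, to disease judged resectable by a minimally invasive approach.

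A reader might infer that the results come only from patients whose operation went well. The documents do not say that. Patients with bleeding, injury, other complications or death but no conversion stay in.

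A reader might also infer that a long incision at reconstruction removes a patient after CSC is known. Step 3 classifies it as a conversion, but the exclusion is limited to conversion during dissection, and reconstruction may fall outside it. The two passages leave this open.

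The 4.4-point figure is the top of an assumed range. It needs 11 of about 44 CSC-positive patients (25%) to convert after the look and no CSC-negative patient to do so. At 5% conversion the corresponding share is 5 of 40 (12.5%). Nothing in the article supports such shares. The morbidity effect concerns a secondary endpoint of a single-arm study. At N = 217 and 20% morbidity the 95% half-width is already 1.96 × √(0.2×0.8/217) = 5.3 points.

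Finally, the article condenses a fuller protocol, and analysis sets and sensitivity analyses may be defined there. Their absence here is not the point. The point is the exclusion rule that the article states, expressly for any reason.

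**Conclusion.** The concern holds in limited form. The stated rule selects on an intraoperative event that occurs after injection and can occur after CSC is scored. It can remove CSC-positive patients, and it removes everyone converted during dissection from 90-day morbidity and mortality. Both are therefore estimated only in operations completed without such a conversion.

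The size is unknown because the documents give no conversion rate. Under the assumptions shown, the CSC rate is understated by about 0 points at one end and by 2.0 points (5% conversion) to 4.4 points (10%) at the other, compared with a target precision of 4-5 points. The morbidity effect is likewise unknown; the figures above are illustrations. The documents do not support a claim that a material bias has been shown, nor that complicated operations in general are left out. The case for changing the rule is that it can act on the outcome itself and is cheap to correct.

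**What to change.** 1. Remove conversion from the exclusion criteria and record it as an intraoperative event with its timing relative to the second NIR look.
2. Primary analysis: include every patient who reached the second look, whatever happens afterwards.
3. 90-day morbidity and mortality: include all injected patients who started the planned resection, converted or not.
4. Report conversions before the second look as CSC not assessable, with best-case and worst-case bounds on the CSC rate.
5. Reconcile the Exclusion Criteria with Step 3 on whether a conversion that occurs only at reconstruction counts.

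The separate exclusion for metastases or organ invasion found at operation is not changed by this.

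The cost is a short amendment. Follow-up data must be kept for converted patients, and the article does not say whether this is done now. Enrolment began in September 2021, so centres should be asked early whether patients already converted can be recovered. The morbidity figure may become slightly less favourable.

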### Sample Size Calculation

The sample size is calculated by considering the estimated incidence of intraoperative change in the surgical conduct when using NIR/ICG technology and targeting the precision of the estimates. Data from the literature indirectly suggest an approximate rate of such an event around 17% (27). Perturbing such assumptions (columns) in a sensitivity analysis, the following scenarios are obtained to get an estimated precision of a certain level (rows) with a confidence level of 1 – alpha = 95%, by using the Wilson approach (31, 32). For precisions between 4% and 5%, the expected range of patients will be between 180 and 400, according to adherence to the initial hypothesis made on the incidence of intraoperative change (**Table 1**). This approach in design captures the uncertainty emerging from the literature and the high variability of papers included in the study.

**Table 1 T1:** Sample size calculation.

Incidence of change in surgical conduct							Precision
**20%**	**19%**	**18%**	**17%**	**16%**	**15%**	**14%**	
6,145	5,911	5,668	5,419	5,163	4,896	4,624	**1%**
2,731	2,627	2,518	2,408	2,294	2,176	2,057	**1.50%**
1,535	1,476	1,417	1,354	1,289	1,223	1,157	**2%**
981	944	906	866	826	782	739	**2.50%**
681	655	629	601	574	543	515	**3%**
501	481	462	442	420	400	379	**3.50%**
382	369	352	337	321	307	288	**4%**
302	291	279	266	253	241	229	**4.50%**
245	234	227	217	207	195	186	**5%**

The scenarios are obtained to get an estimated precision (bold values) of a certain level (rows) with a confidence level of 1 – alpha = 95%.

Computations are performed using the R System and the binomSamSize libraries (33, 34).

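### The lower end of the stated sample size, 180, falls below every 4–5% entry in Table 1 and misses 5% precision at every tabulated incidence

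*Protocol article*

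**What the plan says.** The study is sized on the precision of one proportion, the incidence of a change in surgical conduct (CSC), "with a confidence level of 1 – alpha = 95%, by using the Wilson approach". The assumed incidence is 17%. Table 1 varies it from 14% to 20% ("Perturbing such assumptions (columns) in a sensitivity analysis") and gives the number of patients for precisions from 1% to 5%.

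The section then concludes: "For precisions between 4% and 5%, the expected range of patients will be between 180 and 400", with the place in that range set "according to adherence to the initial hypothesis made on the incidence of intraoperative change".

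Reading from 20% incidence down to 14%, the 5% row of Table 1 is "245 234 227 217 207 195 186" and the 4% row is "382 369 352 337 321 307 288". The 4.5% row lies between them, from 302 down to 229.

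The section names no single number of patients and no single precision. Under Study Design and Setting, the article allows about 3 years for inclusion.

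**The concern.** The sentence and the table should state the same requirement, and they do not. The smallest number in the 4% to 5% rows is 186, yet the text accepts 180. In a single-arm study sized only on precision, the lower end of the range is the figure a reader will take as the acceptable minimum. A minimum rounded downward admits a size that fails the stated criterion. At the protocol's own 17%, Table 1 asks for 217 patients for 5%, which is 37 more than 180.

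Because the section ends in a range and not in a chosen size, the sentence is the only summary of what the study is meant to achieve. That makes its accuracy matter more than it would beside a fixed target.

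**Working it through.** **Inputs**, all from Sample Size Calculation: confidence level 95%, two-sided (z = 1.96); incidence p from 14% to 20% with 17% as base case; precision d from 4% to 5%; Wilson method; stated size 180 to 400. Precision is taken as the half-width of the interval, because that reading reproduces Table 1.

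**Formula.** Wilson half-width for n patients and observed proportion p:

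h = z / (1 + z²/n) × √[ p(1 − p)/n + z²/(4n²) ]

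The required n is the smallest with h ≤ d.

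**Step 1: reproduce Table 1.** All 63 cells agree to within 2 patients. Examples:

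| Incidence, precision | Table 1 | Recomputed |
|---|---|---|
| 14%, 5% | 186 | 186 |
| 17%, 5% | 217 | 216 |
| 20%, 5% | 245 | 245 |
| 14%, 4% | 288 | 290 |
| 17%, 4% | 337 | 338 |
| 20%, 4% | 382 | 383 |

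The table is sound.

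**Step 2: compare the sentence with the table.** The 4% to 5% rows span 186 to 382, and the text says 180 to 400. The lower end is 186 − 180 = 6 patients too low, and the upper end 400 − 382 = 18 too high. The simpler Wald formula, z²p(1 − p)/d², gives 186 to 385, so a change of method does not produce 180.

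**Step 3: precision at the two ends.** For n = 180 and p = 0.17:

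- p(1 − p)/n = 0.1411/180 = 0.000784
- z²/(4n²) = 3.8415/129,600 = 0.0000296
- square root of the sum = 0.02852
- 1 + z²/n = 1.02134
- h = 1.96 × 0.02852/1.02134 = 0.0547, that is 5.47%

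Over the whole grid:

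| Incidence | h at n = 180 | h at n = 400 |
|---|---|---|
| 14% | 5.07% | 3.40% |
| 15% | 5.21% | 3.50% |
| 16% | 5.35% | 3.59% |
| 17% | 5.47% | 3.68% |
| 18% | 5.59% | 3.76% |
| 19% | 5.71% | 3.84% |
| 20% | 5.82% | 3.91% |

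At 180 every value exceeds 5%. Solving h = 5% at n = 180 gives an incidence of about 13.5%, below the lowest column. At 400 every value is under 4%.

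**Step 4: sizes that would match the sentence.**

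- n = 217: 4.99% at 17%, 5.30% at 20%.
- n = 245: at most 4.99% anywhere from 14% to 20%.
- n = 382 (table) or 383 (strict rounding up): 4.0% anywhere from 14% to 20%.

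**The case against.** The best defence is that 180 to 400 is an outward rounding of 186 to 382, offered as an expected range beside a table that gives the exact figures. The low end belongs to the corner with 14% incidence and 5% precision. There the miss is 6 patients, or 0.07 percentage points. The larger gaps at 17% and 20% pair 180 with incidences for which the table itself shows 217 and 245. Most of this stands, and it is why the point is minor. It does not remove the point: even in its own corner 180 does not reach 5%, and a required minimum should not be rounded down.

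The full protocol, which is not shown, may fix one number. That would settle the target, but the mismatch between the article's sentence and its table would remain.

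A reader might go further and infer from "according to adherence to the initial hypothesis made on the incidence of intraoperative change" that enrolment may end anywhere between 180 and 400 in light of the observed CSC rate, so that the interval loses its nominal coverage. The article does not support this. It describes no interim look, re-estimation or stopping rule. The words can equally mean which planning column of Table 1 applies, and the only limit on enrolment that it states is the inclusion period of about 3 years.

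The harm would also be negligible. Suppose one looked after every patient from 180, stopped once the Wilson half-width reached 5%, 4.5% or 4%, and capped at 400. Exact coverage for true incidences of 14% to 20% is then about 94.5% to 96.0%. At fixed sizes of 180, 217, 245 and 382 it is 94.3% to 95.8%.

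**Conclusion.** The point holds as a minor error in the text. The lower bound of 180 misses the stated 5% at every tabulated incidence, by 0.07 percentage points at 14%, 0.47 at 17% and 0.82 at 20%. At the base case it is 37 patients short of the 217 in Table 1 (37/217 = 17%). The upper bound is conservative, and Table 1 needs no correction.

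This rests on precision meaning the half-width of a two-sided 95% Wilson interval, which reproduces the whole table, and on all enrolled patients contributing to the CSC estimate. It implies no bias and no loss of coverage in the CSC estimate. The consequence of stopping at 180 is an interval slightly wider than promised.

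**What to change.** Rewrite the concluding sentence so that it agrees with Table 1 and names one planning size with its precision. Suitable choices are:

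- 245 patients, for a half-width of at most 4.99% at any incidence from 14% to 20%; or
- 217 patients, for 4.99% at the assumed 17%, noting that it becomes 5.30% at 20%.

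If a range is preferred, give it as 186 to 382 and say that the ends correspond to 14% incidence at 5% precision and 20% incidence at 4%. If 180 must stay as a minimum, state its precision as 5.1% to 5.8% over the tabulated incidences.

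The cost is one or two sentences in Sample Size Calculation. All the sizes named lie within the range already stated, and neither Table 1 nor the analysis changes.
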